### Oversight and monitoring

#### Composition of the data monitoring committee, its role and reporting structure

The Ohio State University Center for Clinical and Translational Science (CCTS) established an external DSMB according to NIAID policies. The DSMB is responsible for safeguarding the interests of study participants, assessing the safety and efficacy of study procedures, ensuring data quality, and for monitoring the overall conduct of the study and is independent from the sponsor and any competing interests. The DSMB is asked to make recommendations, as appropriate, to the NIAID about: (1) Efficacy of the study intervention; (2) Benefit/risk ratio of procedures and participant burden; (3) Selection, recruitment, and retention of participants; (4) Adherence to protocol requirements; (5) Completeness, quality, and analysis of measurements; (6) The data and statistical analysis plan; (7) Amendments to the study protocol and consent forms, including whether any new data from other sources affect the equipoise of the study being monitored; (8) Performance of core labs; (9) Participant safety, including review of consent forms; (10) Notification of and referral for abnormal findings; and (11) Participant safety and parent study burden of proposed ancillary studies, including whether the total burden of ancillary studies might compromise the parent study.

The members of the DSMB include independent content experts in pulmonary and critical care medicine, biostatistics, clinical trials, and ethics (some overlapping). The DSMB convened to review the final protocol and DSMB Charter before study initiation and will continue to meet periodically, and not less frequently than annually. The DSMB chairperson will lead each scheduled board meeting and review the prepared board meeting minutes. At each meeting, they will determine whether study progress, data integrity, and safety monitoring warrant continuation of the study and will recommend the study to continue or be terminated, accordingly. The DSMB also approve the data safety plan before the study begins.

It is expected that all DSMB members will attend every meeting and conference call; however, it is recognized that this may not always be possible. A quorum for voting is half of the standing members plus one. A quorum of this DSMB is considered 3 of the 4 standing members, of which the chairperson must be included.

Potential motions of the board meeting include recommendations for either of the following: (1) Study continuation; no change required; (2) Study continuation with stipulation to be formally addressed and approved by the DSMB chair; (3) Study suspension with stipulation to be formally addressed and approved by the DSMB prior to resumption; and (4) Study termination.

The DSMB’s summary report will be reviewed and finalized by the chairperson. The report will then be communicated to the NIAID who will communicate recommendations to the Principal Investigators. DSMB recommendations will be communicated to the IRB in the context of the continuing review process. It is the responsibility of the Principal Investigator to ensure that the IRB is notified by motions requiring termination or suspension of the trial.

An independent Medical Monitor ([name]) has also been appointed. The Medical Monitor is also independent from the sponsor and any competing interests. Their role is to ensure the safety of trial participants throughout the study and to serve as a point of reference for study team members as they evaluate safety events.

#### Adverse event reporting and harms

The DSMB and Medical Monitor shall receive monthly reports from the PI compiling new and accumulating information on AEs and SAEs recorded on appropriate eCRFs or paper CRFs. In addition, the Medical Monitor shall review and make decisions on the disposition of any SAE received by the PI.

#### Frequency and plans for auditing trial conduct

The DSMB will review all safety data after the first 5 patients and at least yearly thereafter during planned DSMB Data Review Meetings. Data for the planned safety reviews will include, at a minimum, a listing of all reported AEs and SAEs, but access to primary data sources (e.g., the RedCAP database) will also be possible. Such data may be provided blinded by treatment group, with the understanding that unblinding may need to occur in a closed session of the DSMB. In addition, the DSMB will be informed of an Expedited Safety Report in a timely manner (within 14 days).

In addition to the pre‐scheduled data reviews and planned safety monitoring, the DSMB may be called upon for ad hoc reviews. The DSMB will review any event that potentially impacts safety at the request of the PI*.* In addition, the following events will trigger an ad hoc comprehensive DSMB Safety Review: (1) Any death that occurs in the study, which is possibly or definitely related to the study treatment regimen (to be reported within 24 h to DSMB); (2) SAEs that are possibly, probably, or definitely related to the study treatment regimen (reported within 24 h to DSMB); Any common trends in unexpected AEs (reported to DSMB within 5 business days). A temporary halt in study recruitment/randomization will be implemented if an ad hoc DSMB safety review is required. Subjects currently in study and tolerating therapy will be allowed to complete their 5-day course. After review of the data, the DSMB will make recommendations regarding study conduct and/or continuation.

#### Procedure for unblinding

Unblinding must be approved by the study Medical Monitor ([name]) unless an immediate life-threatening condition has developed, and the Medical Monitor is not accessible. The care team clinician will notify the PI ([name]) and the study statistician of the unblinding event on the next business day. The emergency unblinding will also be reported to the DSMB. A full account of the event will be recorded, including the date and time of the unblinding, the reason for the decision to unblind, and the name of the individual who made the decision and the names of the Medical Monitor and others who were notified. The reasons for unblinding of a participant’s treatment will be included in the final study report.

Any unblinding the study due to an approved interim analysis, final analysis, or study termination will require written approval from NIAID.

### Dissemination plans

All data will be deposited to the Dataverse that is supported by Harvard University under waivers providing for public availability of data repository starting 12 months after the trial begins and will be deposited every 6 months thereafter. This repository provides metadata, persistent unique identifiers, and long-term access for at least 10 years. Data will be findable for the research community under a unique study identifier through the Dataverse repository. All publications will also be deposited in the Dataverse repository. The study will be assigned a digital object identifier (DOI). This data DOI will be referenced in the publication to allow the research community easy access to the exact data used in the publication.

All data will be stored in common and open formats, such as JPEG, CSV, TXT, or PDF. Information needed to make use of this data (e.g., the meaning of variable names, codes, information about missing data, other metadata) along with references to the sources of those standardized names and metadata items will be included wherever applicable. Project-level metadata will be provided at the time of data deposit using Dryad’s web-based deposit form, which conforms to the DataCite metadata schema, a general standard for describing scientific data. No specialized tools, software, and/or code will be needed to access or manipulate shared scientific data.

Data will be made available as soon as possible or at the time of associated publication or end of the performance period. The research community will have access to data at the end of the grant award or when a publication has been submitted. To request access to the data, researchers will use the standard Dataverse processes. The only controls will be those applied by the repository as per the guidelines for authorized access by the public to maintain data safety and integrity.

The researchers’ intention for scientific data management and sharing will be part of the informed consent process. To protect research participants’ privacy and confidentiality, data submitted to the repository will not include personally identifiable information such as names or addresses. Additional protections, such as the approach for managing Health Insurance Portability and Accountability Act identifiers, will be used for de-identification or to provide a limited data set to minimize the risk of participant reidentification. The study datasets will be collected with Health/Medical/Biomedical informed consent. Consequently, the dataset can only be used for studying health, medical, or biomedical conditions and not for the study of population origins or ancestry.

Intermediate and final data from the SCARLET trial will be disseminated via scientific presentations at appropriate local, regional, national, and international Conferences.

The Ohio State University’s policy on the publication of study results will apply to this trial. Intermediate and final study data will also be submitted for publication in appropriate peer-reviewed journals. Biomarker data may also be submitted to appropriate peer-reviewed journals. Eligibility for authorship for all publications will be based on recommended criteria from the International Committee of Medical Journal Editors [70].

If findings from the SCARLET trial are highly significant, The Ohio State University Media Relations Team (a unit of University Communications) will assist with generation of press articles that will facilitate further dissemination of results to the general public. A website may be established to report progress.

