Key Inclusion and Exclusion Criteria	Inclusion Criteria: (1) Hypoxemic acute respiratory failure plus evidence of active SARS CoV-2 infection (positive for SARS CoV-2 using antigen or PCR test within the 10 days prior to randomization) (2) C-reactive protein > 32 mg/dl Exclusion Criteria: (1) Prisoners (2) Women who may be pregnant, are pregnant, or who are breast feeding (3) Subjects who are unable or unwilling to give written informed consent or to comply with study protocol and who have no legal authorized representative (LAR) available to give consent on their behalf (4) Individuals with a known allergy to citicoline (5) Subjects that are taking medications that contain L‐Dopa, centrophenoxine, or meclofenoxate (6) Individuals with hypertonia of the parasympathetic nervous system (7) Subjects who, in the clinicians estimation, will be unlikely to survive the protocol duration due to imminent and unavoidable risk of death (8) Individuals being treated with extracorporeal membrane oxygenation (ECMO) (9) Individuals with multiple organ failure
Study Type	Single-site, double-blinded, placebo-controlled, and randomized Phase 1/2 dose-ranging and safety study
Date of First Enrollment	7/14/2023
Sample Size	Planned: 80 Enrolled: 15
Recruitment Status	Recruiting
Primary Outcome	A statistically significant difference in lowest recorded S_p_O_2_:F_i_O_2_ ratio on study day 3, at *P* < 0.05
Key Secondary Outcomes	Statistically significant differences (*P* < 0.05) in: (1) Lowest recorded S_p_O_2_:F_i_O_2_ value on study days 1–2 and 4–8, or until extubation (whichever comes first) (2) Lowest Sequential Organ Failure Assessment (SOFA) score on study days 1, 3, 5, and 8 (3) Highest COVID Ordinal Outcomes Scale score on study days 1, 3, 8, 15, and 29 Oxygen-free days through day 28 Ventilator-free days through day 28 ICU-free days through day 28 Hospital-free days through day 28
Ethics Review	Approved by The Ohio State University Biomedical Sciences Institutional Review Board on 3/28/23 [name] [contact]
IPD sharing statement	Plan to share IDP: Yes All data will be deposited to the Dataverse that is supported by Harvard University under waivers providing for public availability of data repository starting 12 months after the trial begins and will be deposited every six months thereafter. This repository provides metadata, persistent unique identifiers, and long-term access for at least 10 years

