### Randomization and blinding

Eligible participants who have provided informed consent will be randomized 1:1:1:1 to 0.5, 2.5, or 5 mg/kg/dose citicoline or placebo. Randomization will be completed in permuted blocks of variable size. Each subject will receive a computer-generated randomization ID number, which will be provided to the research pharmacy, where the appropriate test agent will be prepared. Test agent will be labeled with the ID number and date only.

Patients, treating clinicians, trial personnel, and outcome assessors will be blinded to group assignment until after the database is locked and blinded analysis is completed.

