## Trial status

Protocol version: 4.81, December 5th, 2023.

Date of first enrollment: 14th July, 2023.

Approximate date for completion of recruitment: March 2025.

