## Data Availability

Our ethical and legal responsibility to respect participants’ rights to privacy and to protect their identity will inform our policy for sharing clinical data once the trial has been completed. We will gain informed consent for publication of the dataset from participants at the point of enrollment in the trial. Clinical datasets will not contain any direct or indirect identifiers and participants will remain fully anonymous.

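### The data-release times contradict each other, and the early schedule makes accumulating data of a double-blind trial public at least twice before recruitment is due to end

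*Protocol article*

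**What the plan says.** The early schedule appears twice. Under Dissemination plans, all data are to be deposited with "public availability of data repository starting 12 months after the trial begins and will be deposited every 6 months thereafter". The IPD sharing statement in Table 1 gives the same timing: "starting 12 months after the trial begins and will be deposited every six months thereafter". The dissemination section adds that intermediate as well as final data will be presented at conferences, and that "Intermediate and final study data will also be submitted for publication in appropriate peer-reviewed journals".

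Other statements give later times. Further on, Dissemination plans gives the research community access when the grant award ends or a publication has been submitted, through the repository's request process. It also offers a choice between as early as possible, publication, and the end of the performance period. The Data Availability section speaks of "sharing clinical data once the trial has been completed".

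Two sections bear on confidentiality. Randomization and blinding says that patients, treating clinicians, trial personnel and "outcome assessors will be blinded to group assignment until after the database is locked and blinded analysis is completed". Procedure for unblinding requires written NIAID approval before the study is unblinded for an approved interim analysis, the final analysis or termination.

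**The concern.** The early schedule is dated from the start of the trial, not from database lock or last follow-up. Nothing in Table 1 or Dissemination plans says that treatment allocation is held back, and the only access controls named are those of the repository. Someone following Table 1 would release data while the site is still enrolling.

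This matters even without arm codes. Under Outcomes, a dose is judged safe from the serious adverse events that treating clinicians attribute to it. Under Eligibility criteria, the care team must approve before a patient is approached. Clinicians and prospective participants who can read accumulating safety and oxygenation results may judge attribution or participation differently from those who cannot. If allocation were in the file, the blind would be lost and interim comparisons could be made by anyone. A public release cannot be taken back.

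**Working it through.** The article states no figure on this point, so there is none to reproduce. The check is calendar arithmetic plus an accrual projection.

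**Inputs**
- Release rule: 12 months after the trial begins, then every 6 months (Dissemination plans; Table 1).
- Start: "Date of first enrollment: 14th July, 2023" (Trial status). The start is not defined for the release rule, so registration (31 May 2023, Abstract and Table 1) and ethics approval (28 March 2023, Table 1) were also tried.
- End: "Approximate date for completion of recruitment: March 2025" (Trial status), taken as 1 to 31 March 2025.
- Planned 80, enrolled 15 (Table 1; the count is undated).
- Follow-up to day 29 (Participant timeline).

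**Step 1: release dates**

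| Start used | 12 months | 18 months | 24 months | Before 1 March 2025 |
|---|---|---|---|---|
| First enrollment | 14 July 2024 | 14 January 2025 | 14 July 2025 | 2 |
| Registration | 31 May 2024 | 30 November 2024 | 31 May 2025 | 2 |
| Ethics approval | 28 March 2024 | 28 September 2024 | 28 March 2025 | 2, and a third within March |

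On every reading at least two releases precede the planned end of recruitment.

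**Step 2: patients enrolled at release, even accrual to plan (assumption)**

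Enrolled = 80 × (days from first enrollment to release) ÷ (days from first enrollment to end of recruitment). The denominator is 596 days to 1 March 2025 and 626 days to 31 March 2025.
- First release, 366 days: 80 × 366/626 = 46.8 and 80 × 366/596 = 49.1, so about 47-49.
- Second release, 550 days: 80 × 550/626 = 70.3 and 80 × 550/596 = 73.8, so about 70-74.

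**Step 3: patients enrolled at release, from the reported count**

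Assume that the 15 were counted between 5 December 2023 (date of the protocol version) and 18 May 2024 (publication).
- Counted on 5 December 2023: 144 days = 4.73 months; 15/4.73 = 3.17 per month; 12 × 3.17 = 38 at 12 months; 80/3.17 = about 25.2 months, which is August 2025.
- Counted on 18 May 2024: 309 days = 10.15 months; 15/10.15 = 1.48 per month; 12 × 1.48 = about 18 at 12 months; 80 ÷ (15/10.15) = about 54.1 months, which is January 2028.

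At either rate recruitment would outlast the 24-month release as well, so slower accrual lowers the number of patients in the first release but puts more releases inside recruitment.

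The counts in steps 2 and 3 are upper bounds on complete records, because follow-up runs to day 29 and the Data collection plan locks data only after verification.

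**The case against.** The strongest reply is that early public release is only one of several statements, and that depositing data periodically while opening access later is a possible reading. The later statements on grant end, publication and trial completion do stand, so early release cannot be called the settled plan. They do not remove the problem: the early rule speaks of public availability, is the only one tied to a fixed interval, and stands in the registration dataset.

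A reader might infer that results by arm will be exposed. The article does not support that. Blinding is to group assignment and lasts until lock, data access is set by blinded or unblinded role (Data collection plan), and unblinding needs written approval. Depositing arm codes would breach those rules. What remains is that the release text itself does not exclude allocation. Release of pooled data does not by itself break the blinding rule.

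It is also fair that study staff already see pooled data, since they enter it from the medical record and the principal investigator compiles monthly adverse event reports. The added information for them is small. It may be larger for care-team clinicians outside the study and for prospective participants. Nor does the choice between analysis of variance and Kruskal-Wallis add much to the concern: the article ties it to model assumptions that are checked on the data in any case.

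Intermediate data is undefined and could mean baseline or pooled summaries. The Interim safety analysis section sets a rule for safety only. Other sections let the DSMB consider futility and efficacy, but none provides for public interim results.

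**Conclusion.** The point holds as a conflict between release times, one of which is unsuitable for a double-blind trial that is still enrolling. At least two releases precede the planned end of recruitment whichever start date is used; that finding needs no accrual assumption. As written, the early schedule would make at least pooled outcome and serious adverse event data public, and would breach the blinding and unblinding rules if allocation were included.

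The number of patients affected is uncertain. At 12 months it is about 47-49 of 80 (58-61%) with even accrual to plan, and about 18-38 under the assumed dates for the count of 15. The first range should not be quoted alone, because it ignores the reported enrollment. Any effect on enrollment or attribution is a risk and cannot be sized from the article.

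**What to change.** Reconcile the IPD sharing statement in Table 1, Dissemination plans and Data Availability into one rule. No participant-level, by-arm or intermediate outcome data should be deposited, presented or published until the last day-29 follow-up, database lock and completion of the primary analysis, and the first deposit should be dated from that point. Until then, interim data go only to the DSMB and through required safety reporting. If intermediate data is kept as a term, define it so that it excludes outcome data before lock.

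This is a change of wording and does not touch the design, sample size or analysis. It costs later sharing and needs the funder's agreement. It should be in place before any deposit is made.

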### Ethical considerations and compliance with good clinical practice

This clinical study will be conducted using good clinical practice, as delineated in *Guidance for Industry: E6 Good Clinical Practice Consolidated Guidance*, and according to the criteria specified in this study protocol.

As this study is being performed under a research IND, the PI ([name]) is the sponsor. Both the sponsor and the funding agency (the National Institutes of Health) played a role in trial design. The sponsor will oversee and has ultimate authority over collection, management, analysis, and interpretation of data and writing the final study report. The sponsor will work with the co-PI ([name]) to decide where and when to publish the final study report, which will be done regardless of the trial outcome. A steering committee composed of members of the trial team and representatives from NIAID has been established. This committee meets monthly to discuss progress of the trial and any potential concerns or anticipated changes in trial design and conduct.

Before study initiation, the protocol and the informed consent documents were reviewed and approved by the OSU Conflicts Advisory Committee, the OSU Institutional Biosafety Committee, and the OSU Institutional Review Board (IRB). Any amendments to the protocol or to the consent materials will be approved by the IRB before they are implemented.

Each participant’s privacy and confidentiality will be respected throughout the study. Each participant will be assigned a unique identification number and these numbers rather than names will be used to collect, store, and report participant information. Site personnel will not transmit documents containing personal health identifiers to the study sponsors or their representatives.

